The neonatal particularities of infants born to obese mothers are not well known, partly because the data from the literature comes mostly from obstetric studies that provide only summary information about immediate neonatal morbidity, based on data collected in the delivery room. No available study on this subject has been conducted by a neonatology team focusing on the first days of life. At first look, the fetal and neonatal complications described in pregnancies of obese women appear analogous to those described for the children of women with diabetes during pregnancy, and the current data do not allow the determination that any specific disorder is related to maternal obesity, independently of diabetes. Nonetheless, it appears that the modifications to the intrauterine environment secondary to maternal obesity could by themselves lead to specific fetal and neonatal consequences, as shown by data about malformations. The risk of fetal malformations appears higher among obese, compared to non-obese, pregnant women; these concern primarily neural tube defects but can also affect other organs, including the heart, the gastrointestinal tract, and the lungs [7-11]. Some attribute these malformations to the frequent association between obesity and diabetes, but other studies have shown that obesity is an independent risk factor for fetal malformations [12]. Accordingly, an association with the risks of congenital diaphragmatic hernia and of omphalocele was found, neither generally reported in diabetes [8].

Some studies have shown that obese mothers' newborns have a higher birthweight and that this is related to the mother's preconception BMI (body mass index) and to her weight gain during pregnancy, independently of diabetes [13, 14]. The higher birthweight in the newborns of obese women without diabetes may be associated only with an increase in fat mass, but not lean body mass [15]. The body composition of newborns can be assessed from measurements that allow a reliable estimate of the lean and fat body mass [16]. These measurements include weight and height, from which BMI (weight/height2) and the ponderal index (weight/height3) can be calculated, as well as head circumference and the following skinfold thicknesses: tricipital, bicipital, supra-iliac, and subscapular. Estimates of the fat mass by measurement of these skinfolds and by absorptiometry correlate well [17].

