Leptin is a protein produced mainly by adipose tissue but also by the placenta. Fetal adipose tissue is a major source of leptin, the production of which follows the development of this tissue: the leptin level is low during the first half of pregnancy and then rises strongly during the third trimester. Its production may be regulated by insulin, but also by fetal hypoxia [24]. Maternal leptin does not cross the placenta. The vast majority of placental leptin is released into the maternal circulation, with only a tiny fraction entering the fetus [25]. Some authors consider that the leptin level at birth simply reflects the newborn's body fat mass [26]. Others, however, consider that it is an important factor in fetal growth and development and that its action is independent of that of insulin and of IGF-1 [27-29]. Its mechanism of action on fetal growth nonetheless remains unknown.

Adiponectin is another protein secreted exclusively by adipose tissue. It is paradoxically lower in obese individuals and increases during weight loss. Adiponectin is an important modulator of insulin action and of glucose metabolism — both elements that regulate fetal growth. It is accordingly a possible factor in regulating this growth. Different studies have analyzed the profile of adiponectin expression in newborns as a potential function of in utero growth. The results are often contradictory, but the profile of this expression differs from that observed in adults. That is, levels in newborns are higher than those in adults [30, 31]. Birthweight is thought to be positively correlated with the adiponectin concentrations assayed in the cord blood of preterm infants, growth-restricted newborns, and normal-weight newborns born at term [32]. On the other hand, this concentration may be lower in newborns with macrosomia [33]. Some consider that adiponectin levels are unrelated to fat mass in fetuses, although they are related in adults [34]. Finally, a recent study shows that the umbilical cord adiponectin level is correlated only with height at birth [35]. This hormone may thus act by increasing fetal insulin sensitivity and thereby potentiating the effect of IGF-1. Adiponectin has never been studied specifically in the newborns of obese mothers. Moreover, it has several isoforms (globule-shaped, hexameric forms, and high molecular-weight forms) [36] and their variations may have different metabolic significance [37].

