**3. Study objectives:**

**The principal objective** of this project is to study whether the infants of obese mothers have differences at birth in body composition, assessed by weight and fat mass, compared with the infants of normal-weight mothers. We will focus especially on differentiating the role of maternal obesity from that of her diabetes.

**The secondary objectives** are tostudy:

- the differences in the functioning of adipose tissue of the newborn infants of obese, compared with non-obese, mothers, assessed by leptin and adiponectin assays;
- the relations between the different growth factors, such as IGF-1 and insulin, and the infant's birth weight and fat mass (because hemolysis is frequent in cord blood samples and insulin cannot be assayed in these conditions, insulin will be assessed by an assay of C-peptide, since they are present in equimolar quantities);
- the relations between the maternal metabolic indicators (leptin, adiponectin, glycosylated hemoglobin (HbA1c), fructosamine and blood glucose), the newborn's fat mass (quantity and functioning) and growth factors (C-peptide and IGF-1);
- the relations between the course of newborn's blood glucose level in the immediate postnatal period and the hormone concentrations measured in the umbilical cord blood (C-peptide, IGF-1, leptin, and adiponectin);
- estimation of the rates of perinatal mortality, morbidity, and hypoglycemia.

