**10. Statistics and data management:**

**10.1 Description of the statistical methods to be used, including the timing of any planned interim analyses.**

The study design plans to include two groups of women, obese (BMI 30 kg/m2) and non-obese (18.5 ≤BMI< 25 kg/m2).

- *Principal statistical analyses*

The principal analysis will estimate the role of maternal obesity on the newborn's body composition. We will seek specially to differentiate the attributable portion associated with obesity from that associated with diabetes. The outcome measures will be the sum of the skinfold measurements, the ponderal index, and the birth weight. We will use a covariance analysis model. Besides obesity and diabetes (no diabetes, diabetes treated by diet only, and diabetes treated by insulin), the following potential confounding factors will be introduced into the model: maternal age, hypertension during pregnancy, smoking, parity, newborn's sex, geographic origin, paternal BMI, gestational age at birth, height of father and mother, and the study center. Fetal deaths will be excluded from the analysis.

- *Secondary analyses*

- The respective roles of obesity and diabetes on the functioning of the newborn's adipose tissue, assessed by the cord blood leptin and adiponectin assays, will be estimated by analysis of variance.

- The role of growth factors such as IGF-1 and insulin (the secretion of which will be estimated by the C-peptide assay) on the newborn's body composition will be estimated by linear regression.

- The relations between the maternal metabolic indicators (leptin, adiponectin, glycosylated hemoglobin, and fructosamine) and the newborn's fat mass (quantity and functioning) on the one hand, and the newborn's growth factors (C-peptide and IGF-1), on the other hand, will also be studied by linear regression.

- The rate of hypoglycemia developing in the 48 hours after the birth of infants of obese mothers will be estimated with its 95% confidence interval.

- The rates of perinatal events in the two groups will be compared with Fisher's exact test.

- *Calendar of analyses*

No interim analysis is planned. The analysis will take place 3 years after the study begins.

**10.2 Planned number of study subjects, and planned number of subjects at each study center, with its statistical justification.**

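### Cord leptin and adiponectin levels are analysed as adipose tissue function with no measure of the infant's fat, so a leptin difference cannot separate altered function from more fat

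*Protocol*

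**What the plan says.** The first secondary objective (Protocol section 3) is "the differences in the functioning of adipose tissue of the newborn infants of obese, compared with non-obese, mothers, assessed by leptin and adiponectin assays". Section 10.1, under secondary analyses, gives the matching method: the separate contributions of obesity and diabetes to the "functioning of the newborn's adipose tissue, assessed by the cord blood leptin and adiponectin assays, will be estimated by analysis of variance". Obesity and diabetes are the only factors named. No skinfold, ponderal index, birth weight or hormone-to-fat ratio appears.

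Section 10.1 keeps amount and function apart when it refers to "the newborn's fat mass (quantity and functioning") in the analysis of maternal indicators. The closing list of aims in section 2.1 makes the same split: weight and fat mass are one item, and the fat's production of leptin and adiponectin is another.

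For the principal analysis the method is different: "We will use a covariance analysis model", followed by a long list of covariates.

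Section 2.1 states on leptin: "Some authors consider that the leptin level at birth simply reflects the newborn's body fat mass". On adiponectin it states: "Some consider that adiponectin levels are unrelated to fat mass in fetuses, although they are related in adults". It also cites evidence that the higher birthweight of infants of obese women without diabetes "may be associated only with an increase in fat mass, but not lean body mass".

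**The concern.** If leptin output rises with the amount of adipose tissue, a group of infants with more fat will have higher cord leptin even when each unit of fat behaves in the same way. The planned comparison would pick up that difference, and the wording of the objective invites the reader to take it as a change in function. The reverse can also happen: lower output per unit of fat could be hidden by a larger fat mass.

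What is at stake is the conclusion drawn for the first secondary objective. The protocol sets out to distinguish two constructs and then uses a measure that, for leptin at least, its own background says may not distinguish them. No other planned analysis closes the gap. The regressions in section 10.1 relate growth factors to body composition, or maternal indicators to the newborn's fat and growth factors. None relates cord leptin or adiponectin to the infant's own fat mass within the comparison of obese and non-obese mothers.

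**Working it through.** **Inputs from the Protocol.** Section 10.2: 235 analysed per group, effect size 0.3, power 90%, alpha 5%, and skinfold differences of 0.4 mm (SD 0.95) and 0.5 mm (SD 1.2). Section 10.3: two-sided tests.

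**Input not in the Protocol.** The within-group correlation r between cord leptin and fat mass. It is assumed and shown over a range of 0.3 to 0.8, with 0 as a reference.

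**The plan's own figures.**
- n per group = 2 × (1.960 + 1.282)² / 0.3² = 233.5, so 234 by the normal approximation. The t-test solution is 234.5, so 235 as stated.
- 235 / (1 − 0.24) = 309.2, against 309 stated.
- 0.4 / 0.95 = 0.42 and 0.5 / 1.2 = 0.42, as stated.

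The sample size reproduces and is not in question.

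**Model with no change in function.** Let fat mass F have SD 1 within each group and differ by d between groups. Let leptin be L = r·F + √(1 − r²)·e, with the same equation in both groups. The difference in mean leptin is then r·d in SD units.

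**Chance of a significant raw difference.** With 235 per group the standard error is √(2/235), so the expected test statistic is r·d × √117.5 = 10.84·r·d, and

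P = Φ(10.84·r·d − 1.96) + Φ(−10.84·r·d − 1.96).

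Example: d = 0.42 and r = 0.5 give r·d = 0.21. The expected statistic is 2.28 and P is 62%.

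| Assumed r | d = 0.30: leptin difference | P | d = 0.42: leptin difference | P |
|---|---|---|---|---|
| 0 | 0 | 5% | 0 | 5% |
| 0.3 | 0.09 SD | 16% | 0.126 SD | 28% |
| 0.5 | 0.15 SD | 37% | 0.21 SD | 62% |
| 0.7 | 0.21 SD | 62% | 0.294 SD | 89% |
| 0.8 | 0.24 SD | 74% | 0.336 SD | 95% |

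A simulation (4,000 runs per setting, r = 0.3, 0.5 and 0.7) agreed, giving 16% to 62% for d = 0.30 and 27% to 90% for d = 0.42.

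**Same simulation with fat mass as a covariate.** With fat measured without error, the rate of significant group differences was 4.5% to 5.5%. With a fat measure of reliability 0.8 (assumed), it was about 5% to 13%. The simulation lets fat drive leptin and nothing else, so it shows what measurement error costs but not what happens if leptin also drives fat.

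**Limits of the illustration.** Section 10.2 sets 0.30 as the target for the ponderal index. The 0.42 comes from single skinfolds, comparing mothers with BMI ≥ 25 with those below 25. Neither is an observed fat-mass difference for infants of obese mothers. The calculation compares two groups, whereas the planned model also contains diabetes, which could absorb part of the difference.

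**The case against.** Several counter-arguments have weight.

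- *Functioning has a stated meaning.* Section 2.1 specifies it as production of leptin and adiponectin, and nowhere promises production per unit of fat. The unadjusted contrast is a valid estimate of the total effect of obesity and diabetes on hormone level. This stands: the number is sound, and the problem lies in reading it as function distinct from quantity.
- *The leptin evidence is disputed.* Section 2.1 also cites authors for whom leptin is a growth factor in its own right, independent of insulin and IGF-1. A reader might infer that raw leptin must be higher in the obese group; the Protocol does not establish that. It supports only that more fat is an explanation the planned analysis cannot exclude.
- *More fat is not the stated hypothesis.* A reader might infer that the study predicts more fat in these infants. The hypothesis in section 2.1 is a higher mean birthweight, and the principal objective asks without direction whether weight and fat mass differ.
- *Adiponectin differs.* Section 2.1 describes its results as conflicting and says levels may be lower in macrosomia. With no link to fat there is no artefact, and with an inverse link the bias reverses. The two hormones should not be treated as equally affected.
- *Adjustment has its own risk.* Fat mass arises after exposure. Leptin may contribute to growth, and insulin may act on both. The adjusted coefficient may itself be biased, so it should not decide the matter alone.
- *Covariates may be left to an SAP.* None is shown, and section 4.3 says confounders will be considered, though infant fat is not among them. But the Protocol itself names the method and equates hormone level with functioning, so this is more than omitted detail.

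**Conclusion.** The concern holds for leptin and conditionally for adiponectin. The planned analysis of variance can show whether cord levels differ by maternal obesity and diabetes. It cannot show whether the newborn's adipose tissue functions differently, as opposed to there being more of it.

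On the assumptions above, with identical function, the chance of a significant raw leptin difference is about 16% to 74% for a fat-mass difference of 0.30 SD and 28% to 95% for 0.42 SD. These figures depend on a correlation the Protocol does not give and show how large the risk could be; they do not predict the result.

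A reader might also infer that the leptin analysis merely repeats the primary outcome. That goes too far: at r = 0.5, r² = 0.25, so 75% of leptin variance is unrelated to fat mass. The primary analysis and the sample size are unaffected. What needs to change is how the first secondary objective is analysed and worded.

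**What to change.** 1. Keep the unadjusted comparison of cord leptin and adiponectin, and report it as the total effect of obesity and diabetes on cord hormone level.
2. Add a complementary analysis of covariance with the same factors plus the sum of skinfolds, and repeat it with the ponderal index as a sensitivity analysis.
3. State in advance that altered functioning will be claimed only when both results are shown and the adjusted model supports it. For adiponectin, note that its link with fetal fat is unsettled.

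The cost is small, because section 4.4 already plans skinfold measurements in the newborns and no new data are needed. Three downsides should be written into the plan and the report. Infants without skinfolds drop out of the adjusted model. Skinfolds are an imperfect proxy, so some effect of quantity remains (in the simulation, a false-positive rate of about 5% to 13% at an assumed reliability of 0.8). Fat mass is measured after exposure and may share causes with leptin or be partly driven by it, so the adjusted coefficient is not a clean direct effect.

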**4. Study design:**

**4.1 Principal and secondary outcome measures:**

The principal **outcome measures** are:

- The physical measurements at birth of the infants of obese mothers, that is, the ponderal index, sum of skinfold thickness measurements (skinfolds), and weight. These anthropometric indicators make possible a reliable estimate of the newborn's adiposity (fat mass).

The **secondary outcome measures** are:

- The levels of hormones involved in fetal growth regulation or reflecting the functioning of the fetal fat mass, measured in cord blood: C-peptide, IGF-1, leptin, adiponectin, and its different isoforms.

- The maternal metabolic indicators:

- the existence (or not) of diabetes and the modalities of its treatment
- fructosamine and HbA1c assays at delivery (reflecting mean maternal glycemic control during the weeks preceding the assay)
- maternal leptin and adiponectin levels at delivery, to characterize the maternal adipose tissue.

- Glycemic control in the newborn during the first days of life, assessed by monitoring capillary blood glucose.

-Perinatal events: mortality, malformations, obstetric trauma, perinatal asphyxia, respiratory distress, preterm delivery, and hypoglycemia.

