**4.3 Steps taken to reduce and avoid bias:**

We will recruit control and obese women simultaneously: when a woman is included in the obese group, a non-obese woman will be included in the control group at the same maternity ward within a maximum of 7 days.

A reference midwife will note among the files of women consulting that day the women who could be included as controls because they meet the inclusion and matching criteria. When she identifies a control subject, she will inform her about the study and the protocol; the physician will collect her consent during the visit. This process will be repeated daily until a control woman is recruited.

Matching will be based initially on the obese woman's age (± 3 years), term of the pregnancy (± 2 weeks) and parity (nulliparous and primi- or multiparous).

The following confounding variables will be taken into account in the data analysis: maternal smoking, maternal diabetes, hypertension during pregnancy, geographic origin, paternal height and BMI, and the infant's sex.

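### Perinatal events are compared between groups only by an unadjusted Fisher's exact test, although section 4.3 says unmatched confounders such as smoking and geographic origin will be taken into account

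*Protocol*

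**What the plan says.** Section 10.1, under secondary analyses, states: "The rates of perinatal events in the two groups will be compared with Fisher's exact test". It names no covariate and no pairing for this comparison, and gives no other between-group analysis of these outcomes. Section 4.1 lists them as "mortality, malformations, obstetric trauma, perinatal asphyxia, respiratory distress, preterm delivery, and hypoglycemia".

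Section 4.3, on reducing bias, makes two relevant commitments:
- **Matching.** "Matching will be based initially on the obese woman's age (± 3 years), term of the pregnancy (± 2 weeks) and parity", with the control recruited at the same maternity ward within 7 days.
- **Adjustment.** "The following confounding variables will be taken into account in the data analysis: maternal smoking, maternal diabetes, hypertension during pregnancy, geographic origin", followed by paternal height and BMI and the infant's sex. Nothing restricts this to one outcome.

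Covariates are named only for the principal covariance analysis of skinfolds, ponderal index and birth weight, where "the following potential confounding factors will be introduced into the model". That list contains every factor named in section 4.3.

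**The concern.** Obese and normal-weight women may differ in smoking and geographic origin. Neither is a matching factor, and either may affect preterm delivery, respiratory distress and other events. A crude test has no means of separating such a difference from an effect of obesity. For perinatal events, the named test and the unrestricted statement in section 4.3 therefore cannot both be followed.

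At stake is a set of p-values at the two-sided 5% level that readers may take as evidence about obesity, with no adjusted estimate beside them. Perinatal events are in the study title. Section 2.1 gives as motivation that existing data cannot isolate any disorder due to maternal obesity.

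**Working it through.** **Inputs from the protocol.** Section 10.2: 309 women recruited per group, 10% lost before delivery, 2% fetal deaths. Section 10.3: two-sided 5%. Section 10.7: fetal deaths stay in the perinatal-event analyses.

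**The plan's own figure.** No sample size or power is given for perinatal events. The sample size for the principal analysis reproduces: effect size 0.3, 90% power and two-sided 5% give 234 per group by the normal formula and 235 by the t-test. Then 235/0.76 = 309.2, stated as 309.

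**Number analysed here.** Only the 10% loss applies, because fetal deaths are kept: 309 × 0.90 = 278 per group.

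**Assumptions, since the protocol gives no values.** Obesity has no effect. The event rate is 7% in women without a binary unmatched confounder. The confounder has prevalence c1 in obese women and c0 in controls, and odds ratio OR for the event.

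**Formulas.**
- Event risk with the confounder: q = OR × (0.07/0.93) / (1 + OR × (0.07/0.93)). This gives 10.1%, 13.1% and 18.4% for OR 1.5, 2 and 3.
- Group event rate: p = 0.07 + c × (q − 0.07).
- Rejection rate: the sum of Bin(x; 278, p1) × Bin(y; 278, p0) over all tables (x, y) with two-sided Fisher p ≤ 0.05. The two groups are treated as independent.

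Worked case, 55% vs 25% and OR 3: p1 = 0.07 + 0.55 × 0.114 = 13.3%, p0 = 0.07 + 0.25 × 0.114 = 9.9%.

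**False-positive rate of the Fisher test, 278 per group**

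| Confounder, obese vs control | OR 1.5 | OR 2 | OR 3 |
|---|---|---|---|
| None | 3.3% | 3.3% | 3.3% |
| 35% vs 30% | 3.5% | 3.7% | 4.1% |
| 40% vs 30% | 3.6% | 4.2% | 5.5% |
| 50% vs 30% | 4.1% | 5.9% | 10.8% |
| 55% vs 25% | 5.0% | 8.9% | 20.6% |

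**Direction.** On the risk-ratio scale, the crude ratio is biased by (1 + c1(RR − 1)) / (1 + c0(RR − 1)), where RR is the confounder's risk ratio. With RR 3, prevalences of 50% vs 30% give 2.0/1.6 = 1.25, away from the null. Prevalences of 20% vs 30% give 1.4/1.6 = 0.875, which would mask a harmful effect. The protocol does not indicate which applies.

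**What ignoring the pairs costs.** This was simulated at 272 pairs, which is slightly fewer than 278, for assumed rates of 10% vs 5%. Fisher's power is 54 to 55% at within-pair correlations of 0, 0.05, 0.1 and 0.2. The exact McNemar test has 54%, 56%, 58% and 63%; the mid-p version has 60%, 61%, 64% and 69%. At zero correlation the whole 6-point gap to mid-p comes from the discreteness of Fisher's test, not from pairing.

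**The case against.** **The statement in section 4.3 is kept where it matters most.** Every factor it lists is in the principal model, and the other secondary analyses (analysis of variance, linear regression) name no adjustment either. This stands as a limit on how strongly to call it a contradiction. But those methods can take covariates without being replaced, and a two-by-two Fisher test cannot.

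**The objective is modest.** Section 3 words it as "estimation of the rates of perinatal mortality, morbidity, and hypoglycemia", it is secondary, and it did not drive the sample size. That limits the importance. Section 10.1 nevertheless plans a between-group test.

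**The larger error rates need strong assumptions.** This is correct. With a 5 to 10 point imbalance the rejection rate stays near or below 5%, except for 5.5% in the most extreme of those cases.

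**Stronger readings that a reader might infer.**
- *That the comparison is both confounded and conservative.* Conservatism describes the test without confounding (3.3% here). With enough upward confounding, rejection exceeds 5%, so the comparison as a whole cannot be called conservative.
- *That ignoring the matching biases the result.* One-to-one matching balances age, parity, gestational age at inclusion and ward, so an unpaired test loses some precision but is not confounded by them.
- *That every factor in section 4.3 should be adjusted for here.* Diabetes and hypertension during pregnancy may lie on the path from obesity to the event. Leaving them out of a total-effect comparison is defensible.

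**Conclusion.** The concern holds in a limited form. As written, sections 4.3 and 10.1 disagree for perinatal events, and the only planned comparison cannot separate obesity from unmatched factors such as smoking and geographic origin.

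Under the assumed 7% rate, the false-positive rate runs from about 3.5% with small imbalance to about 21% with 55% vs 25% prevalence and an odds ratio of 3. Event rate, prevalences and odds ratio are all assumptions, and the direction of any bias is unknown. The documents therefore support the statement that the crude test can mislead, not that it will. The pairing is a minor matter of precision. As the analysis is secondary and the remedy simple, this should be corrected, but it does not threaten the principal analysis.

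**What to change.** 1. In section 10.1, for perinatal events common enough to model (for example preterm delivery and respiratory distress), report an adjusted odds ratio with 95% confidence interval from a logistic model, Firth-penalised where events are sparse. Include obesity group, maternal age, parity, center, smoking and geographic origin. Adjusting for matching factors, rather than conditioning on pairs, keeps women whose match is lost.
2. Leave diabetes and hypertension during pregnancy out of this total-effect model. If an effect of obesity apart from diabetes is also wanted for these events, state it as a separate question.
3. Keep crude rates with Fisher's exact test for very rare events, labelled unadjusted and descriptive.
4. Amend section 4.3 to say which confounders apply to which analysis. Without this, the shorter covariate list would still disagree with it.

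**Cost.** A wording change and a little programming; all these covariates already enter the principal model. Section 10.6 requires substantial changes to the analysis plan to be justified in the final report, so the change is cleaner before analysis.

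**Downside.** Rare events support few covariates. The model has at least six coefficients. A 7% rate gives about 0.07 × 556 = 39 events, or roughly 6 per coefficient. A 2% rate gives about 11 events, fewer than 2 per coefficient, so such events stay descriptive.

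Adjustment does not repair the hypoglycemia comparison: under section 4.4, capillary glucose is not routinely tested in normal-weight infants of normal-BMI mothers with negative diabetes screening. That is a separate matter.
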